#### Evaluation of intervention

##### Primary outcomes

Proportion of all patients who have a VL measurement and are virally suppressed (composite outcome) after 12 months of follow up.

##### Secondary outcomes

Proportion of all patients with at least one documented VL in TIER.Net during the trial follow up.Proportion with VL ≥ 50 copies/mL during follow upProportion with VL ≥ 1000 copies/mL during follow up (virological failure)Among patients with VL ≥ 1000:Proportion with a repeat test within 3 monthsTime from first VL ≥ 1000 copies/mL to repeat VL.Proportion switching to second-line ART after two consecutive VL ≥ 1000 copies/mL measured ≤ 3 months apartProportion completing the treatment failure cascade (VL < 50 copies/mL on repeat testing or switch to second line ART)Cost-effectiveness of the intervention compared to current care with respect to the primary outcome (viral suppression at 12 month follow-up) and two secondary outcomes (proportions of patients with VL ≥ 50 copies/mL and VL ≥ 1000 copies/mL)Acceptability, fidelity, adaptation and contexts in the implementation of the interventions

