However, little is known about how these VL guidelines are being used in clinical decision-making in public ART programmes in SSA. In formative research utilising an electronic database, the Three Interlinked Electronic Register (TIER.Net) [9], of a programmatic ART cohort in rural KwaZulu-Natal, we observed infrequent VLM and sub-optimal management of virological failure. The study showed that only 34% of patients had a viral load documented after 12 months on ART. Only 20% of individuals in the cohort were confirmed to have virologic re-suppression or change to second line therapy after virologic failure, and those who changed therapy did so a median of one year after virologic failure [10]. With the expansion in the indications for ART use [11], such delays are likely to have significant deleterious individual and public health impacts through effects on patient morbidity, accumulation of drug resistance [12–14], and persistent risk of HIV transmission in the setting [15].

Findings from this formative research was presented in a series of workshops to healthcare providers, policy makers, researchers and community representatives using good participatory approaches with a view to co-produce health system interventions to address poor VLM. This protocol describes the proposed interventions and their evaluation. We hypothesise that a staff-centred quality improvement package (QIP) and technological augmentation of an existing electronic ART database (TIER.Net) would result in optimal VLM of patients on ART, prompt clinical management of virological failure and an overall improvement in virological suppression.

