#### Augmentation of TIER.Net with a dashboard system

TIER.Net is an electronic database with varying levels of sophistication in both functionality and reports. It ranges from an off-line version of the electronic register to hybrid that is predominantly offline, with synchronisation centrally when bandwidth allows to a networked electronic version of the paper register [9]. The offline version of TIER.Net is in operation in the public ART programmes in which this study will be embedded.

As part of the proposed intervention, VL results will be imported into TIER.Net daily from the National Health Laboratory Service (NHLS) which will be linked to patients in TIER.Net based on multiple exclusive and linked deterministic rules using a combination of variables such as name, surname, sex, date of birth, date of visit, NHLS lab number, facility and folder number. The information contained in TIER.Net will be used to develop a dashboard which will display the following information:The proportion due VL tests as per South African ART guidelines.The proportion with high VLs (VL ≥ 50 copies/mL).The proportion lost to follow-up.Those with confirmed virological failure (repeat VL ≥ 1000 copies/mL after a first VL 1000 copies/mL measured ≥ 3 months apart).

A dashboard has the advantage of displaying a quick visual state of affairs and how this evolves with time. This will incorporate a text messaging functionality that can be used by healthcare workers/viral load champion to communicate with patients.

It is envisaged that these interventions will result in prompt identification of patients who require VLM, and improve clinical management of virological failure thereby improving the quality and efficiency of service delivery.

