#### Evaluation of the intervention impact

TIER.Net has information on HIV-positive individuals on ART including unique South African Identification number, age, sex, date of ART initiation, viral load results and dates, CD4 count results and dates, type of ART regimen, status of the individual (whether still in care, lost to follow up or dead), and dates of clinic appointments. The clinical charts of the 150 participants per clinic who are in the evaluation cohort will be reviewed to extract these baseline data for entry into REDCap. These will be repeated after each participant has completed 12 months of follow up in their clinic/cluster to capture documentation of VL being measured, test data and the results of the VL. These data will be used to evaluate the impact of the intervention on VLM and virological suppression, and on the treatment failure cascade. Data on all clinic visits irrespective of reason for the visit will be extracted from ClinicLink. These will be used to describe patterns of health care use among the trial population. HIV-positive individuals receiving care in the clinics are not the recipients of the quality improvement interventions, which will be focussed on the nurses and systems for delivering care. Hence, interim visits for any intercurrent illness by patients will be managed as per standard clinical care and will not be routinely reported as adverse events.

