#### Evaluation of the trial intervention

The effect of the intervention on the primary outcome (proportion of patients with VL suppression) will be estimated using a two-stage approach based on cluster (i.e. clinic)-level summaries [19]. The cluster-level approach, although less statistically efficient than methods based on individual level regression, is more robust when there are a relatively small number of clusters. Briefly, in the first stage, the proportion with VL suppression in each clinic will be calculated, and logarithmically transformed. In the second stage, the cluster-level summaries will be compared using a stratified t-test to test the null hypothesis of no intervention effect. Since equal numbers of clinics will be allocated to the 2 arms within each stratum, the unadjusted risk ratio (RR) for the intervention effect will be calculated as the ratio of geometric mean proportion with VL suppression for the 5 clusters in each arm. The 95% confidence interval (CI) will be calculated with the variance estimated from the residual mean square in a two-way analysis of variance of the log proportions on stratum and trial arm, incorporating a stratum by trial arm interaction. An adjusted analysis based on cluster-level summaries may also be done to account for covariate imbalance at baseline, using a similar two-stage process. All covariates will be pre-specified in a detailed analysis plan. In the first stage, an individual-level logistic regression will be done, including terms for stratum and all covariates except the intervention effect, and ignoring clustering. After fitting the regression model, a residual for each cluster will be calculated as the ratio of the observed to the predicted number of events. If the intervention has no effect, the residuals of the two arms should be similar on average. In contrast, if the intervention has an effect, we expect the residuals to differ systematically. Therefore, in the second stage, we will compare the residuals between the trial arms using the methods described above; residuals will be log transformed for the analysis. Analysis of the intervention effect on the secondary outcomes will be done using the same approach. A detailed statistical analysis plan will be prepared before to data analysis.

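### Repeat-test, switch and cascade outcomes are compared only among patients with a detected VL ≥ 1000, a group whose make-up can differ by arm because the package is meant to raise testing

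*Protocol article*

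**What the plan says.** The Secondary outcomes section places four outcomes under one condition, "Among patients with VL ≥ 1000": a repeat test within 3 months, time to the repeat test, switch to second-line ART, and completion of the treatment failure cascade. The abstract describes the secondary outcomes as occurring during follow-up, so the natural reading is a high VL found by a test after randomisation.

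Two other outcomes use everyone. The primary outcome is "Proportion of all patients who have a VL measurement and are virally suppressed (composite outcome) after 12 months of follow up", and the first secondary outcome is "Proportion of all patients with at least one documented VL in TIER.Net during the trial follow up". No all-patient version of any failure-management step is listed.

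On analysis, Evaluation of the trial intervention states: "Analysis of the intervention effect on the secondary outcomes will be done using the same approach". That approach compares log clinic-level proportions by a stratified t-test. The optional adjustment is for covariate imbalance at baseline.

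The package is expected to change testing. The Background hypothesises that it "would result in optimal VLM of patients on ART, prompt clinical management of virological failure and an overall improvement in virological suppression". The dashboard section adds: "It is envisaged that these interventions will result in prompt identification of patients who require VLM". The champions' role includes tracing and recalling patients.

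**The concern.** A patient enters the denominator only if tested and found to have VL ≥ 1000. If intervention clinics test more, they detect viraemic patients whose counterparts in control clinics stay undetected. If the package also prevents some viraemia, that changes the group too. The two arms' denominators are then different kinds of patients, and a difference in the proportion retested mixes who was detected with how they were managed. Adjusting for baseline covariate imbalance is not designed to remove this.

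Prompt management of virological failure is one of the three effects the Background hypothesises, and these four are the effectiveness outcomes that measure it. As written, none offers a comparison with the standing of the primary outcome. An analysis plan that follows the outcome definitions would inherit the problem.

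**Working it through.** **The plan's own figure.** The protocol gives no figure for these outcomes. Its headline power for the primary outcome reproduces with the standard unmatched-cluster formula, taking two-sided 5% as assumed:

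- Variance term: 0.5×0.5/150 + 0.77×0.23/150 + 0.20²×(0.5² + 0.77²) = 0.03656.
- Power = Φ(√(4×0.27²/0.03656) − 1.96) = Φ(0.864) = 80.6%, against 80% stated. This is not in dispute.

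**What the planning values imply for testing.** The target of 77% measured and suppressed needs at least 77% tested in the intervention arm. If control coverage were also 77%, suppression among those tested would have to rise from 50/77 = 65% to 77/77 = 100%. At full coverage in both arms it would rise from 50% to 77%. The protocol does not split the effect, but a testing difference is part of the intended mechanism. Formative work found that "only 34% of patients had a viral load documented after 12 months on ART".

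**Illustration 1 (all rates assumed).** Half of viraemic patients are engaged (60% retested once detected) and half disengaged (20% retested), identically in both arms. Only testing differs.

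Conditional proportion = Σ(share × tested × retested) / Σ(share × tested).

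First scenario:
- Control: (0.5×0.80×0.60 + 0.5×0.30×0.20)/(0.5×0.80 + 0.5×0.30) = 0.27/0.55 = 49.1%.
- Intervention: (0.5×0.95×0.60 + 0.5×0.80×0.20)/(0.5×0.95 + 0.5×0.80) = 0.365/0.875 = 41.7%.

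| Tested, engaged/disengaged: control; intervention | Control | Intervention | Conditional ratio | All-patient ratio |
|---|---|---|---|---|
| 80/30; 95/80 | 0.27/0.55 = 49.1% | 0.365/0.875 = 41.7% | 0.85 | 0.365/0.27 = 1.35 |
| 70/40; 90/75 | 0.25/0.55 = 45.5% | 0.345/0.825 = 41.8% | 0.92 | 0.345/0.25 = 1.38 |
| 60/50; 90/85 | 0.23/0.55 = 41.8% | 0.355/0.875 = 40.6% | 0.97 | 0.355/0.23 = 1.54 |

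The last column uses all cohort members as denominator. It moves away from 1 because detection rises, although retesting of detected patients is unchanged.

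**Illustration 2 (varying the direction).** There are 750 patients per arm (abstract). Assume 10% truly have VL ≥ 1000 (75 patients) and half of these are easily reached. The intervention tests 95% of the easily reached and 85% of the hard to reach, 90% overall. Control tests 80%/40% (60% overall) or 60%/8% (34% overall, matching the formative figure). The detected denominators are 45 or 25.5 in control and 67.5 in intervention. Repeat-test probabilities are the same in both arms.

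| Repeat probability, easy/hard | Control 60% tested: control v intervention | Ratio | Control 34% tested: control v intervention | Ratio |
|---|---|---|---|---|
| 0.50/0.50 | 50.0% v 50.0% | 1.00 | 50.0% v 50.0% | 1.00 |
| 0.50/0.40 | 46.7% v 45.3% | 0.97 | 48.8% v 45.3% | 0.93 |
| 0.50/0.30 | 43.3% v 40.6% | 0.94 | 47.6% v 40.6% | 0.85 |
| 0.50/0.20 | 40.0% v 35.8% | 0.90 | 46.5% v 35.8% | 0.77 |
| 0.30/0.50 | 36.7% v 39.4% | 1.08 | 32.4% v 39.4% | 1.22 |

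For 0.50/0.30 at 60% control coverage: control (37.5×0.80×0.50 + 37.5×0.40×0.30)/45 = 19.5/45 and intervention (37.5×0.95×0.50 + 37.5×0.85×0.30)/67.5 = 27.375/67.5. Over all patients this becomes 19.5/750 = 2.6% against 27.375/750 = 3.65%, a ratio of 1.40. At 34% control coverage the all-patient ratio is 2.25.

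The 34% column is a stress case. It describes documented VLs in earlier work, whereas the sample-size section's 50% measured and suppressed under control already requires at least 50% tested overall.

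**The case against.** **Direction.** A reader might infer that a null effect will look like harm. The documents give no retest probability for newly detected patients, so false benefit and no bias remain equally open. The cohort consists of patients on ART for at least 12 months who attend a trial clinic during recruitment. The Discussion attributes poor monitoring largely to staff training, time, lost results and manual capture. If tests are missed for system reasons, newly detected patients may resemble the others. It also leaves open whether the gap is in testing or in recording, so the true testing difference could be smaller than assumed. All of this stands, and it limits the claim to a possibility.

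**Noise.** Take 10% prevalence, 15 viraemic patients per clinic, the first scenario, and k = 0.20 borrowed from the primary outcome. The variance of the log ratio is [0.509/(8.25×0.491) + 0.583/(13.125×0.417) + 2×0.04]/5 = 0.0624. With 6 degrees of freedom (10 clinics, 4 stratum-by-arm cells), the 95% interval around 0.85 is about 0.46 to 1.57. At 20% prevalence it is about 0.52 to 1.38. A single result would probably not be declared harm. The bias nevertheless shifts the estimate whatever its precision.

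**The remedy.** The all-patient version is no measure of management alone: it gave 1.35 to 1.54 with management identical. It would also fall if the package prevented viraemia. This stands, and it rules out using that version by itself as the headline for management.

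**Cascade start.** A reader might infer that the cascade always starts at the first high VL in follow-up, so that a confirmatory test in someone who entered with a known high VL counts as a first test. The protocol states no such rule, and deriving the index result is ordinary analysis-plan detail.

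**Legitimacy of the measures.** Conditional proportions are natural cascade measures, since a repeat test is called for only after a high VL. This supports keeping them, suitably labelled.

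**Conclusion.** The point holds in a limited form. The four failure-management outcomes are conditioned on a detection event that the package is designed to influence, and the protocol compares them as if the groups were randomised. With no true effect on management, the conditional ratio for repeat testing was 0.77 to 0.97 when added patients were harder to retest, 1.00 when similar, and 1.08 to 1.22 when easier. These sizes rest on assumed prevalence, patient mix, testing coverage and retest probabilities. Only the 34%, the 750 per arm and the 150 per clinic come from the protocol, and k = 0.20 is its value for the primary outcome.

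It would go too far to say that the intervention creates the group: it changes who enters it. Nor do the documents support a conclusion that the trial's main result is compromised, because the primary outcome and the any-VL outcome count all patients.

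**What to change.** 1. For the binary steps (repeat test, switch, cascade completion), add a version with all cohort members as denominator: the proportion of all patients who had a detected VL ≥ 1000 and completed the step. This uses the primary outcome's denominator. Label it as combining detection with management, show it beside testing coverage by arm, and do not read it as a pure management effect.
2. Where numbers allow, compare management among patients whose last VL before the intervention was ≥ 1000. The chart review already supplies this: the cohort's charts "will be reviewed to extract these baseline data for entry into REDCap", and those data include VL results and dates.
3. Keep the conditional proportions and the time to repeat test, labelled descriptive and non-randomised.

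The cost is outcome wording and extra tabulation, with no new data collection. The all-patient version has a composite meaning. The baseline-viraemic subgroup will be small: at an assumed 10% prevalence and 34% with a documented VL, 750×0.10×0.34 = 25.5 patients per arm, or about 5 per clinic.

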## Background

Antiretroviral therapy (ART) scale-up in sub-Saharan Africa (SSA) has been rapid with an estimated 16.4 million individuals on ART by the end of 2018 [1]. The increased expansion in the indication for ART use would result in earlier initiation of treatment and if adherence is suboptimal, could lead to virological failure and the likely development of drug resistance. The likelihood of transmission of resistant virus will depend on ART coverage, duration of ART roll-out and the proportion and absolute numbers of individuals with virological failure [2–4]. Conditions that would influence transmission of resistant virus include proportion of failures with resistant virus, time spent on failing regimen, viral load (VL) of patients with resistant virus, fitness of the resistant virus and the transmission probability compared with ART-naïve individuals [2]. The availability of viral load monitoring (VLM) in resource-rich countries, means individual failing treatment are identified early and switched to alternative suppressive ART. In contrast, many sub-Saharan African countries rely on World Health Organisation (WHO) immunological and clinical criteria for identifying treatment failure which has poor sensitivity and specificity [5]. In settings where there is availability of VLM, their effectiveness has been hampered by poor adherence to monitoring guidelines by healthcare providers [6].

South Africa has the biggest HIV treatment programme in the world with 7.7 million individuals living with HIV and 62% currently receiving ART within a stretched health system [1]. VLM has been part of the public ART programme since roll-out in 2004 and requires people living with HIV (PLHIV) initiating ART to have a VL measured at 6 months and 12 months after ART initiation and 12-monthly thereafter if virologically suppressed [7, 8]. Those with a VL ≥ 1000 HIV-1 RNA copies/mL should be retested after 3 months of adherence counselling support, and then either retained on first-line therapy if re-suppressed or switched to second-line therapy if VL ≥ 1000 copies/mL [7].

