### Participants

Gaps in VLM will be identified in HIV-positive patients aged ≥ 16 years who started ART in the previous 15–18 months in any of the 10 trial clinics through a retrospective review of their clinical charts.

The intervention will be evaluated in all patients aged ≥ 16 years who have been on ART for ≥ 12 months during the study’s baseline time period and attend any of the 10 trial clinics during a three-month recruitment period. No exclusion criteria will apply as there will be no individual enrolment to the trial, rather routine clinical data will be used for the evaluation of the outcomes.

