#### Evaluation of the intervention

The effectiveness of the intervention will be evaluated in HIV-positive individuals aged ≥ 16 years attending the trial clinics who have been on ART for at least 12 months at baseline (the evaluation cohort).

AHRI has a clinical research assistant stationed in each of the ten clinics who registers every patient attending the clinic, irrespective of their reason for attendance or HIV status. A database, known as ClinicLink, was developed in-house at AHRI for the registration of clinic visits and reasons for attendance. ClinicLink will be used to identify patients attending the clinic who meet the criteria for inclusion in the evaluation cohort. Based on current clinic attendance, we will need about three months to meet the target sample size of an average of 150 patients per clinic. These individuals will form the basis for the main analyses. In secondary analyses, all patients meeting these criteria who attend one of the trial clinics during the three-month recruitment phase will be included in the evaluation cohort, even if the sample size is exceeded since the target sample size is considered a minimum. If the target sample size is not met within 3 months, we will extend the recruitment phase for another month as necessary.

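### The switching outcome keeps patients already on second-line ART in its denominator, so the reported proportion is too low by a factor that depends on their share

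*Protocol article*

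**What the plan says.** - **Cohort.** The Participants section begins "The intervention will be evaluated in all patients aged" 16 or over with at least 12 months on ART, and adds "No exclusion criteria will apply as there will be no individual enrolment to the trial". The Recruitment section defines the cohort in the same way, as attenders "who have been on ART for at least 12 months at baseline (the evaluation cohort". Neither mentions line of treatment.
- **Denominator.** Under Secondary outcomes, a group of measures is introduced by "Among patients with VL" of at least 1000 copies/mL. Two of them depend on switching. One is "Proportion switching to second-line ART after two consecutive VL" results at or above 1000. The other is cascade completion, met by VL below 50 "copies/mL on repeat testing or switch to second line ART".
- **Care pathway.** The Background describes the pathway from first line only: after a repeat test, patients are "then either retained on first-line therapy if re-suppressed or switched to second-line therapy".
- **Data.** The Data collection section on intervention impact lists "type of ART regimen" among the TIER.Net items and says these data are extracted at baseline by chart review.
- **Analysis.** The Statistical analysis section applies the cluster-level log-proportion method of the primary outcome to the secondary outcomes as well.

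**The concern.** The cohort and the outcome do not fit together. The Background dates the public ART programme to 2004 and reports that some patients in the local formative cohort had changed to second-line therapy. A cohort with no upper limit on ART duration and no regimen condition can therefore be expected to contain second-line patients. Some will have a VL of at least 1000 during follow-up and so enter the switching denominator. They cannot switch to a line they are already on, so each one counts as a non-switcher however the clinic manages them.

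Two things are at stake. The absolute switching proportion, which describes how well failure is managed, is understated. And if the share already on second line differs between arms, the risk ratio moves with no difference in management. Line of treatment is neither the stratification factor nor one of the two restriction covariates in Allocation and blinding, and there are only five clinics per arm.

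**Working it through.** **The plan's own figure.** The only power figure is for the primary outcome: 80% for 50% v 77%, with 5 clinics per arm, 150 patients per clinic and k = 0.20. Alpha is not stated; two-sided 0.05 is assumed from the 95% CI. The usual cluster-trial formula with one added cluster per arm gives:

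- v = 0.50×0.50/150 + 0.77×0.23/150 + 0.20²×(0.50² + 0.77²) = 0.00167 + 0.00118 + 0.03372 = 0.03656
- √[(5 − 1)×0.27²/0.03656] − 1.96 = 2.82 − 1.96 = 0.86, so power is 80.6%

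All 12 rows of Table 1 reproduce within 2 points. No power is stated for switching or cascade completion, so this point changes no sample-size figure.

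**Switching.** Let s be the share of the denominator already on second line and q the switching proportion among first-line patients. Second-line patients contribute no events, so

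reported proportion = (1 − s) × q.

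This holds whether the denominator is everyone with a VL of at least 1000 or only those with two consecutive such results; s is then the share in whichever group is meant. The values of s below, and the true 20% v 40%, are assumptions.

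| s, both arms | reported, control v intervention | risk difference | risk ratio |
|---|---|---|---|
| 0% | 20% v 40% | 20 points | 2.00 |
| 5% | 19% v 38% | 19 points | 2.00 |
| 10% | 18% v 36% | 18 points | 2.00 |
| 20% | 16% v 32% | 16 points | 2.00 |
| 30% | 14% v 28% | 14 points | 2.00 |

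**Unequal shares.** On the log scale each clinic's proportion gains the term log(1 − s). With a common share within each arm, the risk ratio is multiplied by (1 − s_int)/(1 − s_ctl):

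- 10% control, 20% intervention: 0.80/0.90 = 0.89
- 20% control, 10% intervention: 0.90/0.80 = 1.13
- 5% control, 30% intervention: 0.70/0.95 = 0.74
- 30% control, 5% intervention: 0.95/0.70 = 1.36

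**Cascade completion.** Let r be re-suppression on repeat testing and w switching. If second-line patients re-suppress at the same rate r, the reported proportion is (1 − s)(r + w) + s×r = r + (1 − s)×w. The loss is s×w, not s×(r + w). Assume r + w is 0.20 + 0.10 in control and 0.30 + 0.20 in intervention. At s = 20%:

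- control: 0.20 + 0.80×0.10 = 28%, against 30% among first-line patients
- intervention: 0.30 + 0.80×0.20 = 46%, against 50%

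Had second-line patients been unable to complete at all, the figures would have been 24% v 40%.

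**The case against.** The strongest reply is that the protocol never says second-line patients count as non-switchers. Switching to second line presupposes being on first line, and the Background pathway starts there. A condensed article may leave the at-risk group for a conditional secondary outcome to the analysis plan, which is promised but not shown here. That has force: the plan could narrow the group in one line. But the article does state a cohort and a denominator, and taken together as written they include these patients.

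Four further objections stand and limit the point.

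- A reader might infer that cascade completion suffers equally. It does not: VL below 50 on repeat testing also completes it, so neither a ceiling below 100% nor an understatement by the full share applies.
- A reader might object that switching cannot reach 100%. Where the denominator is everyone with a VL of at least 1000, that would be so anyway, since first-line patients who re-suppress are not expected to switch.
- A reader might infer that the risk ratio is expected to be biased. Clinics are randomised, so no difference in share is expected. A chance difference is part of the between-clinic variation that the residual mean square carries into the confidence interval. The optional adjusted analysis might also address it, but the article commits neither to doing it nor to its covariates.
- Restricting by regimen at the first VL of at least 1000 looks natural, but that regimen is observed during follow-up and can be changed by an intervention meant to prompt switching. Patients could then leave the denominator differently by arm.

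**Conclusion.** The point holds for the switching outcome and, in weaker form, for cascade completion. As written, the switching denominator includes patients for whom the event is impossible, and the reported proportion in each arm is reduced by the factor (1 − s). The documents do not give s, so the actual size is unknown; over an assumed 5% to 30%, the relative understatement is the same 5% to 30%. The risk ratio is unbiased when shares are equal. It shifts only through chance imbalance, by 0.89 or 1.13 at an assumed 10% v 20%. For the cascade, the loss is confined to the switching component if re-suppression is similar in both lines. These are secondary outcomes, and the primary outcome, Table 1 and the sample size are unaffected. This is a cheap tightening of a definition, not a threat to the trial.

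**What to change.** Define the switching outcome among patients recorded as on first-line ART at baseline, and state whether the denominator is one VL of at least 1000 during follow-up or two consecutive ones. Report cascade completion for the same first-line-at-baseline group. Show patients on second line at baseline separately, for repeat testing and re-suppression only. Use baseline regimen, not regimen at the first high result, so that membership of the group is fixed at cohort entry.

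The cost is one line in the outcome definitions and a somewhat smaller denominator. No new data are needed, because regimen is already among the items extracted at baseline.
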